### Adherence/termination

As the adherence of medical staff in implementing the interventions is one of the outcomes of this study, the researchers will not intervene in the adherence of medical staff. If participants choose to withdraw, transfer out of the ward, die, or discharge, they will stop receiving the interventions. The reason will be recorded if the patient fails to complete the evaluation during the evaluation period.

### Study outcomes

Delirium positive is defined as the occurrence of delirium assessed by a nurse researcher using the 3D-DST. Enrolled patients will be assessed twice daily for delirium by a nurse researcher using the 3D-DST for the same period of time as the nurses in the wards. Delirium duration, delirium severity, incidence of delirium, length of stay, in-hospital mortality, delirium assessment, delirium prevention, and treatment interventions performed by medical staff will be recorded by the nurse researcher.

The primary outcome of the study is delirium duration: defined as the number of delirium positive days in older adults between admission and death/transfer from the ward.

Secondary outcomes include six aspects.The severity of delirium: defined as the score of the CAM-S scale evaluated by the nurse researcher.Delirium incidence: defined as the percentage of delirium-positive patients accounting for the total number of included patients from admission to death/transfer out of the ward who were assessed by the nurse researcher using the 3D-DST.Length of stay: defined as the total number of of hospital days from admission to the day of death/transfer.Mortality rate: defined as the percentage of patients who died during hospitalization account for the total number of enrolled patients.The rate of adherence to delirium assessment: defined as the number of delirium assessments by the nurse as a percentage of the number of theoretically required assessments between patient’s admission and death/transfer out of the ward.The rate of adherence to delirium prevention and treatment: defined as the number of preventive and treatment interventions implemented by nurses and clinicians as a percentage of the number of theoretically required interventions between patient’s admission and death/transfer from the ward.

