### Sample size

The primary outcome is delirium duration. We expect that the delirium duration of the intervention group will be one day shorter than that of the control group, with a standard deviation of 1.8 [28], α of 0.05, and intraclass correlation coefficient of 0.00001. Our study will be estimated to provide more than 80% power, at least five delirium-positive patients in each group (ward), and 20 delirium-negative patients will be needed. According to our previous study, the incidence of delirium is approximately 10%, with an estimated 10% of patients dropping out during the study, at least 202 older patients will be needed. Patients will be given a detailed explanation of the benefits they will receive from participating in the study to reach the target sample size.

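### The plan does not fix which patients enter the primary comparison of delirium duration (all enrolled or only the delirious), and the stated power above 80% holds on neither reading

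*Protocol article*

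**What the plan says.** Study outcomes, protocol article: duration is "defined as the number of delirium positive days in older adults between admission and death/transfer from the ward". Taken literally, this counts days in every enrolled patient. It does not say whether a never-delirious patient scores zero or drops out of the comparison.

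Sample size, protocol article: the planned effect is "We expect that the delirium duration of the intervention group will be one day shorter than that of the control group". The other inputs are SD 1.8, alpha 0.05 and an ICC of 0.00001. The section claims power above 80%, and for the patients required it says "at least five delirium-positive patients in each group (ward), and 20 delirium-negative patients will be needed". It applies an incidence of about 10% and a 10% dropout and arrives at 202 patients. It does not say whether the 20 negatives are per ward or in total, or whether they enter the duration comparison.

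Statistical analysis names a generalized linear mixed model for the clinical outcomes and a per-protocol principle. Neither settles the population for duration.

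Three further points bear on this. Positive status is determined by the nurse researcher during the stay, after wards are allocated. Incidence is itself a secondary outcome. The Intervention section covers prevention as well as assessment and treatment.

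**The concern.** Days of delirium per enrolled patient and days per delirious patient are different quantities, with different expected differences and standard deviations. The first compares the patients enrolled in the randomised wards. The second compares subsets formed after allocation.

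The protocol hypothesises that 3D-DST improves adherence to assessment and management. If that extends to prevention, 3D-DST may change who becomes delirious. The delirious patients in the two arms would then not be alike, even without any effect on the length of an episode. If mainly short episodes were prevented, mean duration among the remaining cases would rise, and a real benefit could look like no effect or harm.

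The power statement is also at stake: until the population is fixed, more than 80% refers to no defined comparison.

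**Working it through.** **Inputs from the protocol.** Difference 1 day; SD 1.8; alpha 0.05 (two-sided assumed, as sidedness is not stated); ICC 0.00001 (design effect about 1.000, ignored below); four wards, two per arm; five positives per ward; 20 negatives; incidence 10%; dropout 10%; total 202.

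**Input assumed.** Mean duration among delirious control patients is not given; 2 to 5 days is used.

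**The plan's total.** 4 wards × 5 positives = 20, and 20 / 0.10 = 200. The incidence step therefore has a purpose only if positives drive enrolment. Applying the 10% dropout gives 200 / 0.9 = 222.2, so 223; the stated 202 is not reproduced.

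**Which group can have a 1-day effect?** At 10% incidence the all-patient control mean is 0.10 × m, where m is the mean among the delirious. A fall of 1 day needs 0.10 × m ≥ 1, so m ≥ 10 days even if all delirium were abolished. The 1-day effect makes sense only for delirious patients.

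**Reading A: positives only.**
- Required n per arm = 2 × (1.960 + 0.842)² × 1.8² / 1² = 50.9, so 51.
- Available: 5 × 2 = 10 per arm. Standard error 1.8 × √(2/10) = 0.805; 1 / 0.805 = 1.242. Power = Φ(1.242 − 1.960) = 23.6%, or 21.7% with the t distribution.
- From 202 enrolled: 202 × 0.9 × 0.10 = 18.2 positives, about 9 per arm, power 21.7% (t: 19.7%).

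**Reading B: all enrolled, zero for the never-delirious.** After dropout, 202 × 0.9 / 2 ≈ 91 per arm. Difference = 0.10 × 1 = 0.1 day. Variance per arm = p(1.8² + m²) − (pm)², with p = 0.10 and m one day lower in the intervention arm.

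| Control mean m (assumed) | Average SD | Power, 91 per arm | n per arm for 80% |
|---|---|---|---|
| 2 | 0.74 | 14.7% | 862 |
| 3 | 0.95 | 10.5% | 1,427 |
| 4 | 1.20 | 8.1% | 2,275 |
| 5 | 1.47 | 6.7% | 3,405 |

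For example, m = 3: variances 0.10 × (3.24 + 9) − 0.09 = 1.134 and 0.10 × (3.24 + 4) − 0.04 = 0.684. Then 0.1 / √(1.818 / 91) = 0.707 and Φ(0.707 − 1.960) = 10.5%.

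If incidence also fell from 10% to 7%, the difference would be 0.25 − 0.07 × 1.5 = 0.145 day at m = 2.5 and 0.50 − 0.07 × 4 = 0.22 day at m = 5. Power would be about 23% and 19%.

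**Reading C: positives and negatives counted together, undiluted effect.**
- Negatives per ward: 25 × 2 = 50 per arm; 1 / (1.8 × √(2/50)) = 2.778; power = Φ(2.778 − 1.960) = 79.3%. This is the reading closest to the stated power. It gives patients with no delirium days a 1-day effect and SD 1.8, and it implies 5/25 = 20% incidence rather than 10%.
- Negatives in total: 40 patients, 20 per arm, power 42%.

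**Selection under Reading A (illustration, assumed inputs).** Take gamma durations with mean 3 and SD 1.8, prevent 30% of episodes, and leave the rest unchanged. Preventing the shortest 30% raises the mean among remaining cases to 3.76; preventing a random half of the shortest 60% raises it to 3.50. Meanwhile days per enrolled patient fall from 0.30 to 0.07 × 3.76 = 0.26 or 0.07 × 3.50 = 0.245. Prevention at random across durations gives no shift.

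**The case against.** Several stronger readings are tempting, and the document does not support them.

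- *The trial is sized only on delirious patients.* The Sample size section also names 20 delirium-negative patients, and the stated power is approached only when they are counted. What stands is that it mixes the two groups without saying who is compared.
- *A positives-only analysis is planned.* No sentence says so. The literal outcome definition already fits an all-patient count, and a generalized linear mixed model can handle one. The bias is therefore conditional on a restriction that the plan permits but does not state.
- *Incidence is expected to fall.* Incidence is a secondary outcome, but the hypothesis names adherence, duration and severity, and the sample size uses one incidence for both arms.
- *The arms must differ in who becomes delirious.* Both arms receive the same prevention and treatment package and are to be assessed twice daily by bedside nurses; they differ in the assessment tool. Differential selection through better adherence is plausible, not built in.

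The shift to 3.5 to 3.8 days is also an illustration that depends on short episodes being the ones prevented. It contains no effect on the remaining episodes, so it should not be read as subtracting from a 1-day benefit.

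Finally, the exact count model belongs in an analysis plan that is not shown, and the low power overlaps with a plain sample-size error. Both points are fair. Neither removes the mismatch between the stated outcome and the stated sizing basis.

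**Conclusion.** The point holds as an unresolved inconsistency between Study outcomes and Sample size: the outcome is worded for all older adults, while the 1-day effect and the incidence step make sense only for delirious patients. A positives-only comparison would condition on a post-randomisation event and could be biased; direction and size cannot be derived from the document.

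Power above 80% is not delivered on either coherent reading. It is about 22% with 10 positives per arm (two-sided; about 33% to 34% one-sided). It is about 7% to 15% in all patients with 91 per arm, assuming control means of 5 to 2 days, SD 1.8 among the delirious in both arms, and 10% incidence in both arms. A fall in incidence to 7% would raise the latter to roughly 20%, still far below 80%. The 2-day end is a limiting case, because it puts the intervention mean at one day, the shortest possible episode. The figure of about 79% needs the undiluted effect to be applied to patients without delirium.

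**What to change.** State in Study outcomes and Statistical analysis that the primary analysis is the number of delirium-positive days in all enrolled patients, zero if never delirious, using a mixed model suited to counts with many zeros (for example negative binomial, with the exact form left to the analysis plan). Reconcile the per-protocol statement with this population. Report duration among delirious patients next to incidence, labelled as a non-randomised description. Restate the expected difference and power on the all-patient scale, giving the assumed mean duration among the delirious and the assumed incidence in each arm, and say what the 20 delirium-negative patients are for.

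The cost is an amendment and analysis-plan wording. No new data are needed, since the nurse researcher already assesses all enrolled patients twice daily. Because preliminary analyses are scheduled at three months and one year, the amendment should say whether results by arm had been seen when the choice was made. The price is a smaller expected difference and a much lower stated power.

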### Cluster randomization and blinding

Before randomization, the wards that participated in the study will be pair matched according to the specialty. Within each of the two pairs, wards will be randomly assigned (1:1) to the intervention or control group using random numbers generated by the computer, which indicates that each group will contain one neurology and one respiratory ward. The medical staff who will be involved in the study only know the protocol of their ward, but not be aware of the protocol of other wards and the hypothesis of the study. Due to the allocation sequence generating, participants’ enrollment, participants’ assignment, data and outcome collection will be done by a nurse researcher, therefore the protocol will not be blinded to the nurse researcher. However, the nurse researcher and the bedside nurse will be unaware of each other's assessment results of delirium.

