### Statistical analysis

SPSS 22.0 (SPSS Inc., Chicago, Illinois, USA) will be used for statistical analysis. Multiple imputation will be used to fill in missing data using the R software. A *P*-value of 0.05 will be defined as statistically significant. The continuous data will be tested for normality and homogeneity of variance by the "One-Sample Kolmogorov Smirnov Test" and the "Homogeneity of Variance Test". Mean and standard deviation (SD) will be used for normally distributed continuous variables, median and interquartile range (IQR) will be used for continuous variables with non-normal distribution. The rank sum test and *t*-test will be used to compare the demographics and clinical characteristics of different groups. Categorical variables will be expressed in frequency and percentage, and the Chi-square test or Fisher's Exact Test will be used for comparing variables between different groups. The effects on clinical outcomes will be analyzed by a generalized linear mixed model. Subgroup analysis will be performed to eliminate the effect of confounding factors (age, gender, education level, comorbidity, marital status, smoking, drinking, cognitive function, physical function, depression, and comorbidity). Data will be analyzed according to the per-protocol principle. The preliminary analysis will be conducted after the start of the study (three months, one year, close-out).

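### Delirium duration and length of stay are counted only to death or transfer, so an early exit scores as a favourable value and no stated analysis separates it from recovery

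*Protocol article*

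**What the plan says.** In the protocol article, Study outcomes, the primary outcome is delirium duration, "defined as the number of delirium positive days in older adults between admission and death/transfer from the ward". Length of stay in the same section is the total of "hospital days from admission to the day of death/transfer". Mortality is a separate secondary outcome, "defined as the percentage of patients who died during hospitalization account for the total number of enrolled patients". Transfer out of the ward is not an outcome.

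Adherence/termination treats transfer and discharge as two different exits: "If participants choose to withdraw, transfer out of the ward, die, or discharge, they will stop receiving the interventions". Discharge does not appear in the definitions under Study outcomes.

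Statistical analysis has three statements that bear on this:
- "The effects on clinical outcomes will be analyzed by a generalized linear mixed model"
- "Multiple imputation will be used to fill in missing data using the R software"
- "Data will be analyzed according to the per-protocol principle"

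None of them says how a death or a transfer during a delirium episode enters the comparison.

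**The concern.** Fewer delirium days is the hoped-for result; Sample size expects the intervention arm to be one day shorter. A raw count that stops at death or transfer gives a low value for two opposite reasons: the delirium resolved, or the patient was no longer there to be assessed. A patient who dies on the second day of delirium contributes 2 days. A patient who recovers after five contributes 5 and counts as the worse result.

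Length of stay behaves in the same way. It is labelled in hospital days, yet it may end when a patient moves to another ward.

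The Introduction says that delirium raises mortality, and in-hospital mortality is a listed outcome, so deaths are foreseen. If exits during an episode differ between arms, the arm with more of them looks better on the primary outcome for a reason unrelated to recovery.

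**Working it through.** **1. Patients who carry the primary outcome.** Sample size gives five delirium-positive patients per ward, an incidence of about 10%, dropout of 10% and a total of 202. Four wards allocated 1:1 make two wards per arm, so 2 × 5 = 10 delirious patients per arm. From the total, 202 × 0.10 = 20.2, again about 10 per arm; after dropout, 202 × 0.90 × 0.10 = 18.2, about 9 per arm. Because the sample size is stated in delirium-positive patients, I take the duration comparison to be among them.

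**2. Days lost per truncating death (assumed).** The article gives an SD of 1.8 days but no mean duration. I assume a mean of 4 days, with death equally likely at any point of the episode. Mean loss = 4 × 0.5 = 2 days.

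**3. Shift in the arm mean.** Shift = days lost ÷ delirious patients in the arm.

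| Days lost by one extra death | 10 per arm | 9 per arm |
|---|---|---|
| 2 (average under step 2) | 0.20 | 0.22 |
| 3 | 0.30 | 0.33 |
| 5 | 0.50 | 0.56 |

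The bottom row is extreme. Simulating step 2 with a gamma distribution (mean 4, SD 1.8, minimum 1 day), a death removes 5 days or more in only about 5% of cases.

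**4. Expected difference when death rates differ.** Difference = excess mortality among delirious patients × mean loss.
- 10% v 20%: 0.10 × 2 = 0.20 day.
- 10% v 30%: 0.20 × 2 = 0.40 day.
- Equal rates and equal delirium courses: 0.

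**5. Scale.** The standard error of the difference with 10 per arm is 1.8 × √(2/10) = 0.80 day. A shift of 0.2 day is one fifth of the 1-day target and a quarter of one standard error.

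**6. A different model.** Let episodes be geometric with mean M days and let exits have a daily hazard h while delirious. Expected counted days = 1 / [1 − (1 − 1/M)(1 − h)]. Recovery is the same in both arms; h is assumed to be 2% in one and 10% in the other. The SD of the untruncated episode is √[M(M − 1)].

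| M | h = 2% | h = 10% | Difference | SD of episode |
|---|---|---|---|---|
| 2 | 1.96 | 1.82 | 0.14 | 1.41 |
| 3 | 2.88 | 2.50 | 0.38 | 2.45 |
| 4 | 3.77 | 3.08 | 0.70 | 3.46 |
| 5 | 4.63 | 3.57 | 1.06 | 4.47 |

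The direction is the same. The large differences need a fivefold gap in exit hazard and an episode SD about twice the article's 1.8 or more. The rows whose SD lies nearest to 1.8 give 0.14 to 0.38 day.

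**7. Length of stay.** Difference = excess share of early exits × half the stay. With an assumed 5% excess: 0.05 × 7/2 = 0.18 day for a 7-day stay and 0.05 × 14/2 = 0.35 day for a 14-day stay.

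**8. Whether the stated analyses repair it.** Days after death or transfer lie outside the outcome as defined, so they are not missing and imputation does not address them. The per-protocol statement does not say whether early exits are dropped; dropping them would be selection after randomization. A mixed model fitted to the truncated count still takes the low value as favourable.

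**The case against.** **Both arms get the same care package.** Prevention and treatment interventions are common to both arms and only the assessment tool differs, so there is no documentary reason to expect exits to differ. If the tool reduced deaths, truncation would work against the intervention. This stands: the direction of any bias is unknown, and only exits before or during an episode affect delirium duration.

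**Mortality is reported alongside.** An imbalance in deaths would be seen. True, but seeing it does not correct the duration comparison, and transfers would not be seen at all.

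**Stopping at ward exit has a reason.** The ward is the cluster and the intervention ends at transfer; later days could reflect another ward's practice. That supports keeping the primary definition, and I would keep it.

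**This belongs in an analysis plan.** That plan is not shown and may contain a supportive analysis. The definitions themselves, however, are fixed in the article, and they are what make an early death favourable.

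**Stronger readings that a reader might infer.** One is that one or two deaths could produce or hide most of the 1-day effect. Two average deaths shift the mean by about 0.4 day; larger shifts need unusually long losses or exit rates for which the article gives no basis. Another is that length of stay certainly ends at a move between wards. The article does not settle this: Adherence/termination lists discharge apart from transfer, while Study outcomes never mentions discharge, so transfer may be meant to include it.

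**Conclusion.** The point holds in a limited form. As defined, delirium duration and length of stay give a favourable value to a patient who dies or leaves early, and no analysis stated in the article prevents this. Under the assumptions of a 4-day mean episode, a random cut point and about 10 delirious patients per arm, each extra death moves the arm mean of the primary outcome by about 0.2 day against a 1-day target. That is modest beside a standard error of about 0.8 day. The size rests on rates that the article does not give, and there is no bias if such exits are balanced. The documents do not show that exits will differ or which arm would gain. For length of stay, death shortens the outcome on any reading; the ward-transfer part depends on what transfer means.

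**What to change.** - Keep the primary definition of delirium duration.
- Pre-specify one supportive analysis of delirium duration in which in-hospital death ranks worst. Daily delirium status and in-hospital death are already recorded. Days alive and free of delirium over a fixed window would suit less well, because the article describes no delirium assessment after a patient leaves the ward.
- Report by arm how many delirious patients had an episode cut short by death and how many by transfer.
- Analyse length of stay as time to discharge alive, with in-hospital death as a competing event.
- Reconcile Adherence/termination with Study outcomes on whether transfer includes discharge, so that length of stay ends at hospital discharge rather than at a move between wards.

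The cost is a few lines of text, one extra analysis that may disagree with the primary, and discharge dates from hospital records for transferred patients. Enrolment was still open when the article was published, so this could be fixed before the close-out analysis.

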### Participants

The participants are older patients continuously admitted to four general medical wards. Patients should be: 1) age ≥ 65 years old, 2) able to communicate effectively in Mandarin, 3) stay in the hospital longer than two days. Exclusion criteria are: 1) severe hearing or visual impairment, 2) refuse to participate in this study, 3) continuous coma during the study period, 4) severe dementia which is defined as a diagnosis documented in the medical record because such patients cannot be assessed for delirium. This study was approved by the ethics committee of the Capital Medical University and the study hospital. Patients who meet the inclusion criteria will be informed about the study protocol, and written informed consent will be obtained from the older participant or their legal representatives by the first author. Three supervisors (member of the Ethics Committee, administrators of the research program and education department in the hospital) will monitor the accuracy and feasibility of the research process once a year.

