### Intervention and implementation

The intervention includes assessment, prevention, and treatment of delirium implemented by nurses and clinicians (Fig. 3).

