### Data collection

A nurse researcher enrolls the older patients according to the inclusion and exclusion criteria and collect demographic data at admission, including sex, age, ethnicity, education level, marital status, smoking, and drinking. Clinical data includes diagnosis of major diseases, visual acuity level, hearing level, cognitive function, physical function, depression, and comorbidity. The mini-mental state examination (MMSE) is used to assess cognitive function, the total score is 0–30, and a higher score indicates better cognitive function [30]. The Geriatric depression scale (GDS-15) is used to assess depression, the overall score is 0–15, with less than 8 indicating depression [31]. The Charlson comorbidity index (CCI) is used to assess the comorbidity index, and a higher score indicates more underlying diseases in older people [32]. The Modified barthel index (MBI) is used to assess the activities of daily living at admission by the nurse researcher, and a higher score indicates better mobility. Restraint use during hospitalization will also be recorded [33].

The delirium assessment data will be stored in a smartphone with 3D-DST installed, and the data can be exported. Patients' general and clinical data is collected using questionnaires, and the data will be input into SPSS by two researchers and checked for errors. The data is stored by the investigator and is confidential before, during and after the trial. Only the investigators responsible for the outcome collection and supervisors of this study have access to the data according to the protocol.

Prior to the study, a study group is established, all adverse events will be reviewed regularly by the researchers, and a meeting of the researchers will be convened if necessary to assess the risks and benefits of the study. All adverse events will be recorded in detail, properly handled, and followed up until the adverse events are properly resolved. Serious adverse events will be reported to the ethics committee and authorities according to regulations.

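### The secondary outcome called delirium incidence counts any delirium during the stay, including delirium already present at admission, so it does not measure new delirium

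*Protocol article*

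**What the plan says.** All references are to the protocol article.

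- **Study outcomes** defines the measure: "Delirium incidence: defined as the percentage of delirium-positive patients accounting for the total number of included patients from admission to death/transfer". Case status comes from the sentence "Delirium positive is defined as the occurrence of delirium assessed by a nurse researcher using the 3D-DST". Neither sentence asks for new onset, a preceding negative assessment, or a denominator of patients still at risk.
- **Participants** sets the inclusion criteria as "1) age ≥ 65 years old, 2) able to communicate effectively in Mandarin, 3) stay in the hospital longer than two days". The exclusions begin "Exclusion criteria are: 1) severe hearing or visual impairment, 2) refuse to participate in this study, 3) continuous coma during the study period", and the fourth and last is severe dementia. Delirium at admission is not among them. A legal representative may give consent, so a patient who is delirious on arrival can be enrolled.
- **Data collection** lists the admission variables: "Clinical data includes diagnosis of major diseases, visual acuity level, hearing level, cognitive function, physical function, depression, and comorbidity". Delirium status is not one of them, nor is it among the confounders named under Statistical analysis.
- **Study outcomes** also says "Enrolled patients will be assessed twice daily for delirium by a nurse researcher using the 3D-DST". Data collection adds that these ratings are stored and can be exported. The article does not say how soon after admission the first rating is made.
- **Intervention and implementation** gives the scope of the programme: "The intervention includes assessment, prevention, and treatment of delirium implemented by nurses and clinicians". Objectives names the effect on incidence as a secondary objective.

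**The concern.** A measure called incidence, reported for a programme that includes prevention, will be read as the effect on new delirium. Delirium present on arrival cannot be prevented by anything the ward does. Under the stated rule, a patient positive at the first assessment is nevertheless scored as an incident case.

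Two things are at stake. If admission delirium is equally common in both arms, the risk ratio for new delirium is pulled towards 1. If it is not, the difference at admission passes into the outcome as an apparent effect. Imbalance is plausible: there are only two wards per arm, matched on specialty alone, and the nurse researcher who enrols patients knows the allocation (Cluster randomization and blinding). Without admission status by arm, a reader could not tell an effect on new delirium from such an imbalance.

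**Working it through.** **Figures the article gives.** Sample size states 202 patients, a delirium rate of about 10%, 10% dropout, and at least five positive patients per ward. It states no power for incidence and does not say whether the 10% means new or any delirium. The expected number of cases is 202 × 0.9 × 0.10 = 18.2, or about 9 per arm. The stated five per ward gives 5 × 2 = 10 per arm. I use 10.

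**Assumed inputs.** The article gives neither f, the share of control-arm cases present at admission, nor RR, the true risk ratio for new delirium. Both are varied below.

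**Dilution with balanced arms.** Let T be the total control-arm proportion.

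- Control arm: fT + (1 − f)T = T
- Intervention arm: fT + RR(1 − f)T
- Measured risk ratio = f + (1 − f)RR

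| f | true RR 0.50 | true RR 0.70 |
|---|---|---|
| 0% | 0.50 | 0.70 |
| 25% | 0.625 | 0.775 |
| 50% | 0.75 | 0.85 |
| 75% | 0.875 | 0.925 |

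For example, 0.25 + 0.75 × 0.70 = 0.775.

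**Risk difference.**

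- All patients: T(1 − f)(1 − RR)
- Patients delirium-free at admission: T(1 − f)(1 − RR)/(1 − fT)

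The first is (1 − fT) times the second. With f = 50% and RR = 0.50:

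- T = 10% (planning rate): 0.10 × 0.5 × 0.5 = 2.5 points, against 2.5/0.95 = 2.6 points.
- T = 40% (top of the background range in the Introduction): 0.40 × 0.5 × 0.5 = 10.0 points, against 10.0/0.80 = 12.5 points.

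**Power.** Same f and RR, two-sided 5%, 202 × 0.9/2 = 91 evaluable patients per arm (86 or 73 once admission cases are removed), clustering ignored:

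- T = 10%: about 9% as defined, about 14% for new onset.
- T = 40%: about 29% as defined, about 49% for new onset.

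**Imbalance.** Suppose there is no true effect, denominators are equal, and each arm would have 10 positives. Two or three extra admission cases in one arm raise its count by 2/10 = 20% or 3/10 = 30%. In the intervention arm this gives a risk ratio of 1.2 or 1.3. In the control arm it gives 10/12 = 0.83 or 10/13 = 0.77.

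**The case against.** The strongest reply is that the definition is explicit. A reader can see that it counts any delirium, so the fault is largely one of naming. The outcome is secondary, carries no power claim, and is absent from the stated hypothesis, which names adherence, duration and severity. The admission share is assumed. At 10% the risk difference is almost unchanged, and the comparison is uninformative under either definition. These points stand, and they limit the weight of the finding. They do not remove it: incidence is a stated objective, and the rule does not measure it.

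A reader might infer that the primary outcome is spoiled in the same way, because duration also counts from admission. The documents do not support that. The hypothesis and primary objective are to shorten delirium through recognition and management, and the treatment measures include dealing with underlying causes and re-evaluating delirium that does not resolve. Days of delirium present at admission can be shortened, so they belong in duration. What remains there is possible imbalance between arms, as with any prognostic factor. The choice of covariates may properly sit in a fuller document that is not shown.

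Two practical objections also stand. The timing of the first assessment is not given. If it follows some ward care, status at that assessment may already reflect the intervention, and conditioning on it could introduce bias. And recruitment is well advanced (begun September 2020, due to end November 2023) with preliminary analyses planned, so replacing a stated outcome now would invite criticism as post hoc.

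**Conclusion.** The point holds for the secondary outcome only. As written, it is the proportion of patients with any delirium during the stay. Nothing in the article confines it to new cases.

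If any admission cases are enrolled and the arms are balanced, the risk ratio for new delirium moves towards 1. The direction needs no figure for f; the size does. Under assumed shares of 25% to 50%, a true 0.70 becomes 0.775 to 0.85. The loss is mainly on the ratio scale and in power, and at the 10% planning rate the risk difference changes little. If the arms are not balanced, the bias can go either way, and with about ten positives per arm two or three cases are enough to matter. The article gives no evidence that such an imbalance exists.

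**What to change.** 1. Relabel the existing measure *any delirium during stay* and keep it as defined.
2. Add new-onset delirium: a first positive researcher assessment after a negative first researcher assessment, among patients negative at that first assessment.
3. State when the first researcher assessment is made. Use only first assessments made at or close to admission, so that the status is not affected by ward care.
4. Report delirium at that assessment by arm as a baseline characteristic.
5. Optionally, run a sensitivity analysis of duration adjusted for that status. The primary definition stays as it is.

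The cost is small. The twice-daily ratings are already stored, so no new data are needed where the first was made early enough. The denominator shrinks slightly: with T = 10% and f = 50%, from 91 to about 91 × 0.95 = 86 per arm. The new-onset analysis must be dated as added before the final analysis. Because delirium fluctuates, one negative rating does not prove absence at admission, so some misclassification will remain and should be acknowledged.
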